**Fig. 1 Fig1:**
[figure not shown]
Flow chart of patients included in the NAVISTROKE trial

**Fig. 2 Fig2:**
[figure not shown]
User-centred approach for the design of the intervention

**Fig. 3 Fig3:**
[figure not shown]
Logic Model of Navistroke program

### Control (treatment-as-usual, TAU)

Patients in the control group will be followed-up according to usual practices that are not driven by the protocol or a structured process. Usually, the hospital discharge report is given to the patient at discharge and sent by postal mail to the general practitioner. Discharge prescriptions are explained to the patient and, if necessary, a social worker and/or occupational therapist may assist the patient or caregiver with administrative issues and preparation of home adaptations. After discharge, patient and caregiver support is based on the needs assessment made by the general practitioner and on patient and caregiver requests.

### Measurement of patient outcomes

The outcomes and data collection calendar are presented in Table 2 and linked with the intervention components in Fig. 3.

**Table 2 Tab2:** Study schedule

		Patient			Caregiver			Instrument
Timing	Inclusion	1 week	6 months	12 months	1 week	6 months	12 months	
Baseline information	x							
PRIMARY OUTCOME								
Participation			x					The Stroke Impact Scale
SECONDARY OUTCOMES								
Participation				x				The Stroke Impact Scale
Quality of life		x	x	x	x	x	x	The Stroke Impact Scale and Short Form-12
Anxiety and depression		x	x	x	x	x	x	The Hospital Anxiety and Depression scale
Fatigue, sleep quality and sleepiness		x	x	x				The Pichot scale, the Pittsburgh scale and the Epworth scale
Zarit burden scale						x	x	The Zarit burden scale
PROGNOSIS OUTCOMES								
Stroke recurrence				x				Reported by the patient and/or caregiver and validated by checking the hospital discharge report
Death				x				
Rankin				x				The modified Rankin Score
Cognitive disorders				x				The Montreal Cognitive Assessment scale
ACCESS TO CARE OUTCOMES								
Consultations and hospitalizations		x	x	x				Reported by the patient and/or caregiver and a copy of medical prescriptions will be collected
Maintaining hospital discharge prescriptions		x	x	x				
Therapeutic persistence		x	x	x				
Occupational status				x			x	Reported by the patient and/or caregiver
Social isolation		x	x	x				The Social Support score Questionnaire
Patient activation Measure		x	x	x				The Patient activation Measure
Maintenance at home or institutionalization				x				Reported by the patient and/or caregiver
Satisfaction with the support received upon return home				x			x	Reported by the patient and caregiver through a structured questionnaire
Feeling of information about stroke and medical and social care			x	x		x	x	

#### Primary outcome

Patients’ participation at 6 months measured by the score obtained in the “participation” dimension of the stroke-specific quality of life scale: SIS 6 months after discharged home [29]. Participation is defined by the International Classification of Functioning, Disability and Health, as an individual’s involvement in life situations in relation to health conditions, body functions or structures, activities, and contextual factors [30]. Participation restrictions are problems an individual may have to fulfil his or her roles and engage in meaningful activities. SIS licence will be obtained before the first inclusion.

#### Secondary outcomes

Participation at 12 months: participation score at 12 months after discharged home (SIS). Quality of life at 6 and 12 months: scores of the other dimensions of the SIS at 6 and 12 months: force dimension, manual function, activities of daily living/instrumental activities of daily living (ADL/IADL), mobility, communication, emotions, memory/thinking, as well as global recovery.

Anxiety and depression scores: change of anxiety and depression scores between discharge home and 6 months, and discharge home and 12 months, measured by the Hospital Anxiety and Depression Scale (HADS) score [31]. Fatigue, sleep quality, and sleepiness: changes in fatigue level measured by the Pichot scale [32], sleep quality measured by the Pittsburgh scale, and sleepiness level measured by the Epworth scale between discharge home and 6 months, and discharge home and 12 months. Epworth scale licence will be obtained before the first inclusion.

Prognosis at 12 months after discharge home: stroke recurrence within 12 months, reported by the patient and/or caregiver and validated by checking the hospital discharge report; unscheduled hospitalisations or emergency room visits within 12 months of discharge from hospital to home reported by the patient and/or caregiver and validated by checking the hospital discharge report; m-RS at 12 months; death at 12 months reported by the caregiver; cognitive disorders at discharge to home and at 12 months, measured by the Montreal Cognitive Assessment (MOCA) scale [33, 34].

Prevention of cardiovascular risk factors: last known blood pressure, LDLc, and glycaemia values, as well as smoking status, physical activity, and body mass index at baseline, 6, and 12 months; these data will be collected by interviewing the patient or in the electronic medical record.

Access to care and social services at 12 months: consumption of care (consultations and hospitalisations) and perceived social aids; these data will be collected by interviewing the patient.

Maintain of the hospital discharge prescriptions at 6 and 12 months (persistence): 6 and 12 months maintenance of secondary treatments for stroke prescribed at discharge, and reasons for discontinuation if applicable; these data will be collected by interviewing the patient and a copy of medical prescriptions will be collected.

Occupational status at 12 months: return to work will be defined by working at least one day per week (10% full-time employment), and occupational status will be characterised as either resumption of the same professional activity, professional reclassification, adapted working time, or invalidity / early retirement.

Social isolation: social isolation at discharge, and at 6 and 12 months thereafter measured by the Social Support Questionnaire 6 [35]

Patient activation: Patient Activation Measure (PAM-13) score at discharge, 6, and 12 months [36]. PAM-13 licence will be obtained before the first inclusion.

Maintenance at home or institutionalization at 12 months.

Satisfaction with the support received upon return home, measured at 12 months by a structured satisfaction questionnaire developed for the study (Additional file 1).

Feeling informed: Feeling informed about stroke and medical and social care at 6 and 12 months through a structured questionnaire investigating perception on quality, understandability, and relevance of information provided by healthcare professionals (Additional file 1).

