
## Objectives

The main objective of the trial is to assess the impact of a patient-centred post-stroke transition programme, combining an Internet information platform and telephone follow-up by a case manager, on changes in the level of patient participation, evaluated by the Stroke Impact Scale (SIS), 6 months after their return home compared to usual care. The transition programme aims to empower patients and their caregivers, and help them to identify, understand and use the available medical and medico-social services according to their needs to improve their recovery. Secondary objectives are to study the efficacy of the programme on the following patient-reported outcomes: patients’ level of activation, quality of life, anxiety, depression, fatigue, and sleep quality at 6 and 12 months; on patients’ functional prognosis, attainment of targeted cardiovascular risk factor objectives, healthcare access, as well as occupational and social functioning at 12 months. We will also measure the efficacy of the programme on informal caregivers’ burden, quality of life, anxiety, depression, and occupational and social functioning. A process evaluation of the intervention implementation will be conducted using a mixed-method approach based on the Medical Research Council guidance [17, 18]. Semi-structured interviews will be conducted to understand the barriers and facilitators perceived by patients and the case manager.

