### Data collection

Data will be collected from the stroke unit medical charts by external research assistants (from the public health department). For each patient included in the trial, a case report form will be completed with his/her characteristics (age, sex, medical history, comorbidities, treatment, diagnosis, initial stroke severity as assessed by the National Institutes of Health Stroke Scale (NIHSS) at admission, pre-stroke autonomy as assessed by the pre-stroke m-RS).

Patients will be contacted within one week of discharge to home, as well as 6 months and 12 months thereafter for the collection of outcomes. This will be done by telephone [39] by trained research assistants of the study coordinating centre. Research assistants are experienced in stroke patient follow-up by telephone using the standardised scales used for this study. However, training by a stroke neurologist will be conducted before study implementation to ensure standardisation of data collection. Prior to each call, patients will receive the questionnaires by postal or email (or by hand at discharge) so that they can be read and pre-populate the questionnaires prior to the call. Patients will be given the choice of postal or email at inclusion. The data collected are listed in Table 2.

We will precisely detail support received by patients in the control group to describe the usual practices during the study.

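### The last-known rule for blood pressure, LDLc and glycaemia lets a value from the index stay stand as a 6- or 12-month outcome

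*Protocol article*

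**What the plan says.** The protocol article, under Secondary outcomes, describes a risk-factor outcome made up of "last known blood pressure, LDLc, and glycaemia values", "as well as smoking status, physical activity, and body mass index at baseline, 6, and 12 months". On the source it says: "these data will be collected by interviewing the patient or in the electronic medical record". It gives no earliest admissible date, no window around 6 or 12 months, and no rule for a patient who has had no measurement since leaving hospital.

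Other sections bear on how that rule works in practice:

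- Data collection says of the outcome contacts: "This will be done by telephone [39] by trained research assistants of the study coordinating centre". No study measurement of blood pressure or blood values is described at 6 or 12 months.
- Randomization places allocation before hospital discharge.
- Objectives lists "attainment of targeted cardiovascular risk factor objectives, healthcare access, as well as occupational and social functioning at 12 months" among the secondary aims.
- Measurement of patient outcomes states that "The outcomes and data collection calendar are presented in Table 2", and Data collection states that "The data collected are listed in Table 2". Table 2 has no row for blood pressure, LDLc, glycaemia, smoking, physical activity or body mass index. Its nearest entry is the generic baseline-information line at inclusion.

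**The concern.** A last-known rule is a carry-forward built into data capture. A patient tested during the index stay and not since has a last known value that predates discharge and may predate randomisation. Entered at 6 or 12 months, it looks like a follow-up result but can reflect little or nothing of the programme.

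Two consequences follow. First, such values carry no treatment effect, so they pull the observed difference between arms towards zero. Second, whether a newer value exists depends on contact with care, which the programme is meant to increase. If it succeeds, the arms could differ in how often the outcome is stale, and the comparison would then mix risk-factor control with frequency of measurement.

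The rule acts before any missing-data method, because a stale value is not recorded as missing. Unless measurement dates are captured, a later analysis plan cannot separate old values from current ones.

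**Working it through.** The documents give no figure for these outcomes, so there is no stated result to reproduce. The first step is a reading of the text; the second is an illustration on assumed inputs.

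**Reading.** Set side by side: allocation before discharge (Randomization), values by interview or from the record with no date limit (Secondary outcomes), and telephone contacts (Data collection). Together they admit an index-stay value at 6 or 12 months when nothing newer exists. If the closing time points in the sentence are read as governing only smoking, activity and body mass index, the three last-known values have no stated time point at all, which does not help.

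**Inputs.** From Sample size: 170 patients and 20% attrition, so 170 × 0.8 / 2 = 68 per arm. Assumed, not in the documents: the stale share f in each arm; the change d, in SD units, between the hospital value and follow-up, equal in both arms; staleness unrelated to the patient's own value; two-sided 5% test, normal approximation.

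**Dilution, equal stale share f in both arms.** Observed effect = δ(1 − f). Power = Φ(δ(1 − f)/√(2/68) − 1.96), with √(2/68) = 0.1715 and the SD held at 1. For δ = 0.5 SD:

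| f | observed effect (SD) | power |
|---|---|---|
| 0 | 0.50 | 83% |
| 10% | 0.45 | 75% |
| 20% | 0.40 | 65% |
| 30% | 0.35 | 53% |
| 40% | 0.30 | 42% |

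At 30%: 0.5 × 0.70 = 0.35, and 0.35/0.1715 − 1.96 = 0.08, so power is about 53%.

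**Bias with no true effect, unequal stale shares.** Spurious difference = (f_control − f_intervention) × d. Its standard error is √((v_I + v_C)/68), where v = 1 + f(1 − f)d² in each arm. With 10% stale in the intervention arm:

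| stale in control | d = 0.5: difference, rejection rate | d = 1.0: difference, rejection rate |
|---|---|---|
| 10% | 0; 5.0% | 0; 5.0% |
| 20% | 0.05 SD; 5.9% | 0.10 SD; 8.5% |
| 30% | 0.10 SD; 8.8% | 0.20 SD; 19.3% |
| 40% | 0.15 SD; 13.7% | 0.30 SD; 36.7% |

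For 30% and d = 1.0: difference (0.30 − 0.10) × 1.0 = 0.20; v_I = 1.09, v_C = 1.21; standard error √(2.30/68) = 0.184; ratio 1.09; rejection rate 19.3%.

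**The case against.** The strongest reply is that this is condensation. Look-back windows and date fields usually sit in the eCRF specification or the analysis plan; the article describes a study-specific eCRF and promises a detailed plan before database lock. A natural reading is also the most recent value available at each contact, and the text does not prescribe reuse of an inpatient value. This stands in part. The text permits the stale value rather than requiring it, and the full protocol may close the gap. But the article states a definition, not merely an omission, and an analysis plan can repair it only if dates were recorded.

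Several stronger readings are tempting, and the documents do not support them:

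- **That stale values are in fact more common in the control arm.** This follows only from the trial's own hypothesis. No testing frequency is given for either arm. Under the Control section, patients still have a general practitioner who receives the discharge report and assesses needs. If the arms are tested equally often, no bias arises under the null, only dilution.
- **That all the risk-factor variables are affected.** The last-known wording governs blood pressure, LDLc and glycaemia. Smoking, physical activity and body mass index are listed separately and can be asked about at each call.
- **That the objective will have no follow-up data because Table 2 lacks the row.** Secondary outcomes itself names baseline, 6 and 12 months. Table 2 also leaves out other items given in the text, such as the cognitive assessment at discharge. The mismatch is editorial.
- **That "attainment of targeted cardiovascular risk factor objectives" contradicts an outcome listed as values.** Attainment can be derived from values; the derivation is detail that an article may leave out.

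**Conclusion.** The point holds for three secondary variables. As written, the definition allows a pre-discharge value to be analysed as a 6- or 12-month outcome. The harm that does not depend on any difference between arms is dilution: with 30% stale in both, a 0.5 SD effect falls to 0.35 SD and power from 83% to 53%. Bias between arms is conditional on the programme changing how often patients are tested. Over the assumed range it is 0.05 to 0.30 SD, and its direction depends on which arm is tested more and on how values move after the stay. All stale shares and changes are assumptions; with a small gap or a small change the bias is negligible. The primary outcome and its analysis are untouched. The reason to act is that the repair is cheap at data capture and may be impossible afterwards.

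**What to change.** - Record in the eCRF the measurement date of every blood pressure, LDLc and glycaemia value, at each time point.
- State that a value counts at 6 or 12 months only if it was taken after discharge and within a pre-specified window around that time point. The sponsor should choose the window; the documents give no basis for a particular width.
- Treat values outside the window as missing under the trial's missing-data method.
- Report the proportion with an in-window value by arm, next to the comparison.
- Add the risk-factor row to Table 2 so that it agrees with Secondary outcomes (editorial).

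The cost is a date field, one derivation rule and a table row. The drawback is more missing values, and that missingness may itself depend on arm and on contact with care. The rule therefore does not remove the problem; it makes it visible, and the comparison should be read alongside the availability figures.

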### Statistical analysis

Categorical variables will be presented using numbers and percentages, and quantitative variables using mean and standard deviation or median and interquartile range according to their distribution.

Group difference in the SIS Participation domain score at 6 months after hospital discharge will be analysed using a linear model adjusted on the stratification factors (centre and presence or caregiver). The primary analysis will be performed in accordance with the intention-to-treat principle (an imputation method for missing data will be used when appropriate). In a modified intention-to-treat analysis and per-protocol analysis, patients who died before 6 months or those with stroke recurrence before 6 months will be excluded. Change in the SIS participation domain score between 6 and 12 month after discharge will be compared between groups using linear mixed effects model. The model will include patients as random effect, time (6 and 12 months), group (TAU or intervention) and an interaction effect of treatment group × time as fixed effects after controlling for the stratification factors.

Continuous secondary outcomes will be assessed in a similar way. Categorical data will be analysed using logistic or survival models. For non-repeated continuous and binary measurements, ordinary linear regression and logistic or Cox proportional-hazards models will be used when appropriate.

A detailed statistical analysis plan will be made prior to database lock. Analysis and reporting of the results will follow the CONSORT guidelines for reporting randomised controlled trials [45]. Analyses will be conducted using SAS software (version 9.4; SAS Institute Inc., Cary, NC, US). All tests will be two-sided and carried out at the 5% level of significance.

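### As written, the model for continuous secondary outcomes does not use the baseline blood pressure, LDLc, glycaemia and body mass index that the protocol collects, which costs precision but causes no expected bias

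*Protocol article*

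**What the plan says.** Under Secondary outcomes, the protocol article lists the cardiovascular risk factors as "last known blood pressure, LDLc, and glycaemia values", followed by "smoking status, physical activity, and body mass index at baseline, 6, and 12 months". On the source it says: "these data will be collected by interviewing the patient or in the electronic medical record".

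The Statistical analysis section gives one repeated-measures model in full, for SIS participation: "The model will include patients as random effect, time (6 and 12 months), group (TAU or intervention) and an interaction effect of treatment group × time", these entering "as fixed effects after controlling for the stratification factors". Those factors are centre and presence of a caregiver. Two extensions follow:

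- Continuous outcomes: "Continuous secondary outcomes will be assessed in a similar way".
- Categorical outcomes: "Categorical data will be analysed using logistic or survival models".

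No baseline term is named in the mixed model, in the logistic and survival models, or in the ordinary regression planned for outcomes measured once. The section also says that a detailed analysis plan will be written before the database is locked.

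**The concern.** The two-time structure suits SIS participation, which the study schedule (Table 2) lists by name only at 6 and 12 months. It does not suit outcomes that the protocol itself defines at three times. Carried over unchanged, the model has no place for the first measurement, either as a time level or as a covariate.

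A patient's own earlier value is usually among the best predictors of a later blood pressure, LDLc, glycaemia or body mass index. Leaving it out puts between-patient variation that could have been explained into the residual, and widens the interval for the group difference. The sample size was set for SIS participation alone, so nothing in the plan secures precision for the risk factors. If the baseline term is not fixed in advance, the choice between raw, change and adjusted analyses is also left open in an open-label trial.

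**Working it through.** **1. The plan's own figure.** Inputs from Sample size: difference 15, SD 27, two-sided alpha 0.05, power 90%.

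- n per group = 2 × (1.960 + 1.282)² × 27² / 15² = 68.1, rounded up to 69 (normal approximation). The t-based solution is 69.06, rounded up to 70. The stated 70 per group is reproduced.
- For 20% attrition, 140 / 0.8 = 175 and 140 × 1.2 = 168. The stated 170 lies between them.
- Expected completers: 170 × 0.8 = 136, or 68 per group.

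No figure is stated for the risk factors, so there is none to reproduce for them.

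**2. Outcome against model.**

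| | Continuous risk factors (Secondary outcomes) | Model (Statistical analysis) |
|---|---|---|
| Times | baseline, 6 and 12 months | 6 and 12 months |
| Baseline value | collected | not named |
| Covariates | – | centre, caregiver |

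**3. Cost of leaving out the baseline.** Let ρ be the correlation between the baseline and follow-up value. The document gives none, so the range below is an assumption. Scale the outcome to SD 1 and take 68 per group with complete data.

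- Without baseline, at one follow-up time: SE = √(2/68) = 0.171.
- With baseline as covariate: SE = 0.171 × √(1 − ρ²), ignoring the negligible cost of estimating one more coefficient.
- Difference detectable at 90% power = (1.960 + 1.282) × SE.
- Equivalent number of patients without adjustment = 136 / (1 − ρ²).

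| Assumed ρ | 1 − ρ² | Variance reduction | SE | Detectable difference (SD) | Equivalent patients |
|---|---|---|---|---|---|
| no baseline | 1 | – | 0.171 | 0.56 | 136 |
| 0.3 | 0.91 | 9% | 0.164 | 0.53 | 149 |
| 0.5 | 0.75 | 25% | 0.149 | 0.48 | 181 |
| 0.7 | 0.51 | 49% | 0.122 | 0.40 | 267 |

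**4. Why a covariate and not a change score.** With equal variances at both times, the variance of a change from baseline is 2(1 − ρ) relative to the raw value: 1.4, 1.0 and 0.6 at ρ = 0.3, 0.5 and 0.7. The adjusted values are 0.91, 0.75 and 0.51, lower in each case. At ρ = 0.3 a change score is worse than ignoring the baseline. The form in which the baseline enters is therefore worth stating.

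**The case against.** The strongest reply is that this is detail for the analysis plan. The article condenses a fuller protocol, announces that plan, and extends the SIS model only loosely. A similar model could use each outcome's own times or add a baseline term. A reader might infer that the baseline values will be discarded; the text does not say so. What stands against the reply is that the section is not silent. It lists time levels and covariates and then applies that approach to the continuous secondary outcomes. An analysis plan that followed it to the letter would leave the baseline out.

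Four further objections narrow the point, and all are right.

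- **Not every risk factor goes through this model.** Smoking status, and physical activity if categorical, go to logistic or survival models. For these the two-time mismatch does not arise; it remains true only that no baseline term is named.
- **The objective is framed differently.** Objectives speaks of reaching risk-factor targets, among the outcomes set at 12 months. That is naturally a yes/no outcome at one time, and the variance calculation above does not apply to it directly.
- **The timing of the baseline is not stated.** A reader might take it as fixed before randomisation. Table 2 puts baseline information at inclusion but has no risk-factor row, and Randomization says only that allocation precedes discharge. The intervention starts after the return home, so a pre-randomisation baseline is likely, but it is an inference.
- **No bias follows.** A reader might infer that chance baseline differences bias the comparison. Under randomisation they do not in expectation, and the standard error already allows for them.

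**Conclusion.** The point holds as a minor one. For blood pressure, LDLc, glycaemia and body mass index, the method as written does not use a baseline value that the protocol collects.

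The cost is precision: a residual variance that adjustment would lower by 9%, 25% or 49% at an assumed correlation of 0.3, 0.5 or 0.7. The low end is plausible for blood pressure and the laboratory values, since the most recent available reading may be old. The patient equivalents also assume that all 136 completers have the value at baseline and follow-up, which interview and record data may not deliver.

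The primary outcome, its model and the sample size are not touched.

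**What to change.** Add to Statistical analysis, and carry into the analysis plan:

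- Blood pressure, LDLc, glycaemia and body mass index are modelled at 6 and 12 months, with the outcome's own baseline value as a covariate alongside the stratification factors.
- The baseline value is the one recorded at inclusion, before randomisation.
- The logistic models for smoking status, for physical activity if categorical, and for any 12-month target-attainment outcome adjust for the corresponding baseline status or value.

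The cost is two or three sentences before database lock. No new data are needed, and the sample size does not change.
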